### Navigator services

Relatives randomized by family to Study Arms 3 and 4 have access to the Family Health Navigator, via phone/email/ videoconference, who can help them use the website, answer questions, and order genetic testing via Color. In addition to responding to requests for help from relatives, the Navigator can also follow up with relatives in Arms 3 and 4 proactively to encourage them to complete study tasks (e.g., complete their baseline survey; consider clicking the link to go to Color’s website to learn more about genetic testing).

## Recruitment and randomization

### Patient trial enrollment and family cluster randomization

Following invitation by the Georgia and California registries, interested patients can visit the University of Michigan-hosted study website to view and complete the guided web study sign-up process, which includes reviewing the online consent form and typing their name to electronically sign the informed consent document and creating an account on the website (to permit return at any time during the study window). Signature on the consent document indicates enrollment in the trial. We expect that approximately 20% of eligible and invited patients will enroll, for an expected total *n* = 412 patients enrolled in the randomized control trial (RCT). After enrollment, patients are randomized at the level of the family cluster (meaning that a patient and all of their relatives are randomized as a unit) into one of four trial arms that vary across two features of the intervention: (1) the level of personalized family genetic risk navigation support (online platform only vs. online platform + human navigator support) and (2) the cost of the genetic test option offered to relatives ($50 vs. free). Randomization is done using a computer program, with participants randomized to one of the four study groups using a random permuted-block design stratified by study site (Georgia and California).

Randomization is concealed from study participants; enrolled patients and relatives are not aware that their family has been randomized into one of four trial arms and provided a different intervention experience than the other study participants. Concealment is necessary for this study so that (a) the trial can observe differences across the trial arms without negatively impacting study enrollment and biasing the study, and (b) study participants do not experience unnecessary negative emotional reactions. The results of a pilot study have demonstrated that concealment can be effective – we did not observe a toxic or detrimental effect to enrollment for pilot study participants offered the $50 trial arm experience. There is no usual care arm in this study – all participants, regardless of randomization, receive the virtual intervention that includes education, assistance with family communication, and heavily discounted at-home testing for enrolled relatives.

### Relatives trial recruitment

Relatives are recruited to the study through the patient participants as part of the patient’s participation in the trial. Patients provide contact information for each first-degree (biological parent, sibling, or biological child) or second-degree (biological half-sibling, aunt, uncle, nephew, niece, grandparent, or grandchild) relative *whom the patient wishes to invite to the study*. As randomization for this study has already been conducted at the time of patient-level enrollment and is concealed from participants and potential participants as described earlier, methods of inviting relatives differ by study arm:

**Patients in Arms 1 and 2** can invite relatives via email only.**Patients in Arms 3 and 4** can invite relatives via email and have the option to ask the Stanford Family Health Navigator to reach out by telephone and/or email to discuss the study with relatives.

*Email invitation*: Patients provide each relative’s name and email address and then review the draft email invitation. Portions of this invitation can be personalized (optional) by the patient for each relative prior to sending. Email invitations can be sent in both English and/or Spanish and are sent to the relative’s email address (as provided by the patient) via the trial platform. The email invitation includes: (1) a greeting from the patient inviting them to the study (customizable); (2) a brief description of the study; (3) a telephone number to call with questions or concerns; (4) a study website link for them to visit to learn more and enroll in the trial; and (5) their unique Access Code (study ID) (which can be linked back with the index patient in order to enable analysis of the entire family unit). A modified Dillman approach to encouraging trial enrollment is programmed into the study platform and sent via a series of email and/or text reminders to the relative at various timepoints.

#### Navigator invitation

Patients in Arms 3 and 4 can also ask the Family Health Navigator to help invite their relatives. Whether or not to involve the Navigator is on a per-relative basis. If the patient chooses Navigator invitation, they will also be asked to provide a phone number for that relative.

Relatives who have been invited with Navigator assistance receive email reminders encouraging enrollment as described above. In addition, the Navigator supplements these auto-emails with phone calls and/or personal emails to encourage enrollment. The Navigator routinely monitors the project dashboard and will not follow up with relatives who have already enrolled.

Regardless of study arm, all invited Relatives eventually receive an Invitation Email containing a clickable link to the GIFT Study website and the Relative’s unique Access Code. The study is described to relatives according to the family’s randomization assignment (study arm) and the fact of randomization assignment is concealed. Both patients and the Navigator can re-send email invitations as needed.

We expect that patient participants in the study (*N* = 412) will have on average a total of eight first-degree (biological parent, sibling, or biological child) and/or second-degree (biological aunt, uncle, nephew, niece, grandparent, or grandchild) adult relatives and that patients will be willing to provide contact information (email address) for three of those relatives (*N* = 1236).

### Relatives trial enrollment

Interested invited relatives visit the University of Michigan-hosted website for more information and complete a brief Eligibility Screener to confirm their eligibility for the study before entering the guided web study sign-up process, which includes typing their name to electronically sign the informed consent document and creating an account on the website (to permit return at any time during the study window). Signature on the consent document indicates enrollment in the study. Overall, we anticipate of those invited that 30% will enroll for a total *N* = 371. Relatives are unaware of their trial arm and experience an enrollment and the intervention consistent with the arm into which their family has been randomized.

## Summary sample size estimates

Table 2 summarizes the expected sample sizes for both Patients and Relatives in the GIFT Study revised prior to completion of patient enrollment (updated to clinicaltrials.gov 11/22/2024). Table 3 and 4summarizes the sample sizes for both Patients and Relatives that we expected prior to launch of the trial.

**Table 2 Tab2:** Sample size summary estimates revised prior to completion of patient enrollment

Study phase	Sample Size
**Patients**	
Initial Patient Sample Selected	4,300 (approximate)
Respondents to PIC Survey	2,358 (expected response rate = 55%)
Pool of Patients eligible for GIFT Study Invitation	2,030 (86% of PIC survey respondents)
Patient GIFT Study Participants	412 (expected enrollment rate = 20%)
**Relatives**	
Relatives invited to the GIFT Study	1,236 (3.3 relatives per enrolled patient)
Relative GIFT Study Participants	371 (expected enrollment rate = 30%)

**Table 3 Tab3:** Sample size summary estimates prior to launch of the trial

Study phase	Sample Size
**Patients**	
Initial Patient Sample Selected	5,250 (approximate)
Respondents to PIC Survey	3,150 (expected response rate = 60%)
Pool of Patients eligible for GIFT Study Invitation	2,930 (93% of PIC survey respondents)
Patient GIFT Study Participants	880 (expected enrollment rate = 30%)
**Relatives**	
Relatives invited to the GIFT Study	3,520 (4 relatives per enrolled patient)
Relative GIFT Study Participants	1,584 (expected enrollment rate = 30%)

### Measures

**Table 4 Tab4:** Endpoints by study objectives

Objectives	Endpoints	Justification for Endpoint
**Primary Aims and Hypotheses**		
**Primary Aim**: To determine the independent effects of the two virtual platform design features on relatives’ receipt of genetic testing. We hypothesize that increased genetic risk navigation support and the availability of lower cost testing will increase the proportion of 1st and 2nd degree relatives reported by patients on baseline survey who complete genetic testing through the study platform (**primary outcome**).	**Family Genetic Testing Fraction**: The proportion of each enrolled patient’s first and second-degree relatives who receive Color genetic testing through the GIFT platform. For each enrolled patient, this will be calculated as the number of enrolled relatives who obtain a genetic test result from Color (complete the genetic testing process) via the GIFT Study divided by the number of relatives reported on the baseline PIC survey. The endpoint of interest is the presence (as opposed to the absence) of a test result (e.g., positive, uncertain, negative) on a quarterly report from Color Health. Assessed six months after the final relative enrolls in the study.	This is the most inclusive and pragmatic outcome relevant to cascade testing in practice and has high internal validity- that is, it is assessed uniformly across all trial arms. Providing six months for relatives to complete the Color testing process is pragmatic and based on observations made in our preliminary work with Color.

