### Primary Aim

**To determine the independent effects of the two virtual platform design features on relatives’ receipt of genetic testing.** We hypothesize that increased genetic risk navigation support and the availability of lower cost testing will increase the proportion of first- and second-degree relatives reported by patients on baseline survey who complete genetic testing through the study platform (primary outcome).

### Secondary aim 1

To determine the independent effects of the two virtual platform design features on the proportion of relatives invited by each patient to enroll in the study. We hypothesize that increased genetic risk navigation support and the availability of lower-cost testing will increase the proportion of first- and second-degree relatives reported by patients on a baseline survey who are invited by the patients to initiate GRE through the study platform (secondary outcome).

### Secondary aim 2

To determine the independent effects of the two virtual platform design features on cancer patients’ assessment of communication with their relatives about hereditary cancer and genetic risk evaluation. We hypothesize that increased genetic risk navigation support and the availability of lower-cost testing will substantially improve cancer patients’ assessment of their communication with relatives about hereditary cancer and genetic risk evaluation (secondary outcome).

### Secondary aim 3

To determine the independent effects of the two virtual platform design features on relatives’ receipt of a formal cancer genetic counseling session in practice. We hypothesize that increased genetic risk navigation support and the availability of lower-cost testing will increase the proportion of relatives enrolled in the trial that complete formal genetic risk evaluation with a clinician, after GIFT study participation.

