### Navigator services

Patients randomized to Study Arms 3 and 4 also have access the Stanford Family Health Navigator, via phone, email, and/or videoconference. The Navigator can help them use the website, answer questions, and invite family members to participate in the study. In addition to responding to requests for help from patients, the Navigator can also follow up with patients in Arms 3 and 4 proactively to encourage them to complete study tasks (e.g., invite more relatives). These communications listed here occur independently of the UM-hosted website.

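### The primary endpoint's calculation rule does not confine tested relatives to the baseline-reported set that the aim and the denominator use, and no rule covers unlisted relatives

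*Protocol article*

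**What the plan says.** The article describes the primary outcome in three places, and the sets of relatives differ.

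- **Aim** (Primary Aim section, repeated in the first column of Table 4): the "proportion of first- and second-degree relatives reported by patients on baseline survey who complete genetic testing through the study platform". Here the tested are a subset of those reported at baseline.
- **Calculation rule** (Table 4, endpoint column): the formula is "the number of enrolled relatives who obtain a genetic test result from Color (complete the genetic testing process) via the GIFT Study divided by" a count of relatives taken from the PIC survey. The denominator is tied to the baseline list and the numerator is not.
- **Model** (Analysis plan, Primary Aim): a random-intercept binomial regression whose trials are the eligible relatives. The target population is the eligible relatives whom the index patient identifies, with no time of identification given.

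Relatives enter after the family has been randomized. Relatives trial recruitment has the patient give contact details for each first- or second-degree relative "whom the patient wishes to invite to the study". The Patients section has the patient type in a name and email address for each. Eligibility criteria screens on kinship, age, vital status, residence and recent clinical testing, but not on whether the relative was reported on the PIC survey. In Arms 3 and 4 only, the Navigator may follow up with patients "proactively to encourage them to complete study tasks (e.g., invite more relatives".

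For Secondary Aim 1, Table 4 divides the number of invited relatives by the number reported on the PIC survey, again without limiting the numerator to that list.

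**The concern.** A proportion analysed with a binomial model needs every success to come from among the trials. The Table 4 rule does not guarantee this. A relative who was not reported on the PIC survey, but is later invited, enrolled and tested, raises the numerator and leaves the denominator unchanged. It is normal for a numerator to accrue after randomization. The difficulty is accrual from outside a denominator fixed at baseline.

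Two things are at stake. First, the model can fail: a family with two reported relatives and three tested has three successes in two trials, which the likelihood cannot accept, and the article has no rule for that case. Second, the meaning of the effect becomes unclear. If unlisted relatives were added more often in one arm, part of the estimated difference would reflect a longer list of relatives and not a higher proportion of the baseline relatives tested, which is what the aim asks about.

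**Working it through.** **1. The plan's own figure.** The article states power of 0.80 at an odds ratio of 1.5 with about 400 families. Inputs (Sample size calculations and Assumptions): 8 relatives per family, ICC 0.15, alpha 0.05 (two-sided assumed).

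- Design effect = 1 + (8 − 1) × 0.15 = 2.05.
- Effective relatives per factor level = (400/2 × 8)/2.05 = 1,600/2.05 ≈ 780.
- No-Navigator margin of Table 5 = (10% + 13%)/2 = 11.5%. An odds ratio of 1.5 gives 16.3%, and power is 0.785.
- $50 margin = (10% + 15%)/2 = 12.5%. An odds ratio of 1.5 gives 17.65%, and power is 0.812.

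The stated 0.80 reproduces. It neither supports nor refutes the point, because it takes the tested to be a subset of the denominator.

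**2. The wordings side by side.**

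| Place | Who can be a success | Denominator |
|---|---|---|
| Primary Aim | relatives reported at baseline | relatives reported at baseline |
| Table 4 rule, primary | any enrolled relative with a Color result | relatives reported at baseline |
| Table 4 rule, Family Invite Fraction | any invited relative | relatives reported at baseline |
| Analysis plan, primary model | relatives who are tested | eligible relatives, time not stated |

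The second and third rows do not make the numerator a subset of the denominator, and the eligibility and invitation rules do not close the gap. The fourth row does not settle it, because it does not say whether eligible relatives are counted at baseline or as the patient identifies them.

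**3. How much it could matter (illustration).** The documents give no rate of unlisted tested relatives, so the range is assumed. Let e be the excess of such relatives per Navigator family, over the other arms. With 8 relatives in the denominator, the fraction rises by e/8. Take 11.5% testing among listed relatives in both Navigator levels, so there is no true difference in the baseline set. The Navigator difference in Table 5 is 15% − 10% = 18% − 13% = 5 points.

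Table 2 sets the scale: 371 enrolled relatives/412 families = 0.90 enrolled per family.

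| e (assumed) | Added points, e/8 | Apparent Navigator rate | Apparent odds ratio | e as share of 0.90 enrolled | Rejection rate |
|---|---|---|---|---|---|
| 0 | 0 | 11.5% | 1.00 | 0% | 0.044 |
| 0.05 | 0.625 | 12.1% | 1.06 | 6% | 0.07 |
| 0.1 | 1.25 | 12.75% | 1.13 | 11% | 0.12 |
| 0.2 | 2.5 | 14.0% | 1.25 | 22% | 0.33 |
| 0.4 | 5.0 | 16.5% | 1.52 | 44% | 0.84 |

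The last column comes from a simulation with 3,000 replicates per row, 412 families of 8 and ICC 0.15. Listed relatives follow a beta-binomial distribution, unlisted tested relatives are Poisson in Navigator families only, and family fractions are compared by a t-test at two-sided 0.05. It is simpler than the planned model and serves only to show scale. At e = 0.1 the excess is 0.1 × 206 ≈ 21 relatives across the Navigator families.

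**The case against.** The strongest reply is that the outcome is already restricted. The aim appears in the same Table 4 row as the calculation rule and limits the outcome to relatives reported at baseline, and a binomial model presupposes a subset. No sentence says that unlisted relatives are counted. This stands to the extent that counting them is one reading and not a stated intention. It does not remove the problem: the article gives an explicit formula, and that formula does not match the aim.

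A second reply is that the survey instrument, the invitation screens and the full protocol are not shown and may settle the matter. They may. The point, however, is not that detail is missing but that two statements of the primary outcome in this article disagree.

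A reader might go further and infer that unlisted relatives inflate the Navigator effect. The documents do not support that:

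- Encouragement to invite more relatives is fully consistent with inviting those already reported. Relatives trial recruitment expects about eight adult relatives per family and contact details for three, which leaves about five uninvited.
- The Discussion reports fewer invitations than expected, not families outrunning their lists.
- The larger assumed rates are high beside Table 2: 0.2 per family is about 22% of expected enrollment, and 0.4 is 44%.
- Extra tests prompted by a Navigator would be a real randomized effect on tests per baseline relative. The rejection rates above are therefore false-positive rates only for the question the aim poses.

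Nor may just any relative enter: the kinship, age, vital status, residence and recent-testing criteria all apply.

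**Conclusion.** The primary endpoint is internally inconsistent. The aim confines the tested to relatives reported at baseline, the Table 4 rule does not, and the model names a different denominator. The Family Invite Fraction has the same gap. As written, the rule permits successes without trials and, in a small family, more successes than trials.

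The size is unknown. Under the stated assumptions (8 relatives per family, excess confined to Navigator families), 0.1 unlisted tested relatives per family would add 1.25 points, a quarter of the 5-point Navigator difference in Table 5. That rate is already about 11% of expected enrollment per family, and nothing in the documents shows that it occurs or that it differs by arm. The finding is a contradiction to reconcile in the primary endpoint, not a demonstrated bias.

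**What to change.** - State in Table 4 that a success, tested or invited, counts only for a relative within the set reported on the PIC survey.
- Match invited and enrolled relatives to that set individually where possible. Where it is not, cap the count for each relationship type at the PIC-reported number. A cap bounds the total but does not identify who was listed, so it is the fallback. The platform already holds reported family information for tailoring and the screener confirms kinship, but the article does not say that relationship type is recorded for every relative; this should be checked.
- Use one baseline-defined denominator in both Table 4 endpoints and in the analysis plan models. If it is restricted to eligible relatives, say that eligibility is determined from baseline information.
- Report unlisted invited and tested relatives separately by arm, with a sensitivity analysis that includes them in both numerator and denominator.

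The cost is revised endpoint wording, a small matching step and perhaps a slightly lower observed fraction. Unlisted relatives stay eligible for the study and for testing. The Discussion says that relative invitation and enrollment is ongoing, so the rule can still be fixed before the final outcome assessment.

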**Secondary Aims and Hypotheses**		
**Secondary Aim 1**: To determine the independent effects of the two virtual platform design features on the proportion of relatives invited by each patient to enroll in the study. We hypothesize that increased genetic risk navigation support and the availability of lower cost testing will increase the proportion of 1st and 2nd degree relatives reported by patients on a baseline survey who are invited by the patients to initiate GRE through the study platform (secondary outcome).	**Family Invite Fraction**: The proportion of each enrolled patient’s relatives who are invited to join the study. For each enrolled patient: Number of invited relatives / Number of relatives reported on baseline PIC survey Assessed 91 days after the final patient enrolls in the study.	This objective will illuminate how the trial features influenced patients’ willingness to invite eligible relatives. There will be complete ascertainment and uniform measurement across all trial arms. Assessment will occur on Day 91 after the final patient enrolls in the study because patients have 90 days to invite relatives.
**Secondary Aim 2**: To determine the independent effects of the two virtual platform design features on the cancer patients’ assessment of communication with their relatives about hereditary cancer and genetic risk evaluation. We hypothesize that increased genetic risk navigation support and the availability of lower cost testing will substantially improve cancer patient’s assessment of their communication with relatives about hereditary cancer and genetic risk evaluation (secondary outcome).	**Assessment of Family Communication Scale**: A 20-item scale with responses on a 5-point Likert from “not at all true” to “very true.” Items assess patients’ capacity, opportunity, and motivation to communicate with family members about their genetic test results. The outcome is continuous, and we will measure the change in mean score from baseline to follow-up survey. A greater difference between timepoints will indicate greater improvement in the patient’s assessment of their communication with relatives. Assessed at two time points: baseline PIC survey and Patient Six-Month Follow-up Survey.	This is an important patient-centered outcomes that will illuminate improvements to our next generation initiatives.
**Secondary Aim 3**: To determine the independent effects of the two virtual platform design features on relatives’ receipt of a formal cancer genetic counseling session in practice. We hypothesize that increased genetic risk navigation support and the availability of lower cost testing will increase the proportion of relatives enrolled in the trial that complete formal genetic risk evaluation in their medical practice within six months after enrollment.	**Relative Receipt of Formal Genetic Risk Evaluation** Single survey question (mark all that apply) with 3 potential responses. “Yes, Color” and “Yes, outside of Color” will indicate receipt of formal GRE. See Appendix F for details. Assessed in the Relative Six-Month Follow-Up Survey	This is an important relative-centered outcomes that will illuminate improvements to our next generation initiatives.

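### Secondary Aim 3 claims randomized effects but compares only relatives who enrolled, a group formed after randomization that the navigator can alter

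*Protocol article*

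**What the plan says.** The Objectives (Secondary aim 3) and Table 4 word the aim as the effect of the two randomized design features. Both take enrolled relatives as the denominator. The Objectives expect that the features "will increase the proportion of relatives enrolled in the trial that complete formal genetic risk evaluation with a clinician", and Table 4 expects that they "will increase the proportion of relatives enrolled in the trial that complete formal genetic risk evaluation in their medical practice". The outcome is one survey question: "Assessed in the Relative Six-Month Follow-Up Survey".

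On timing, the section on relatives' recruitment says that "randomization for this study has already been conducted at the time of patient-level enrollment" and that "methods of inviting relatives differ by study arm". Arms 1 and 2 use email only. In Arms 3 and 4 the patient may also ask for the navigator, relative by relative, and for those relatives "the Navigator supplements these auto-emails with phone calls and/or personal emails to encourage enrollment". The patients' Navigator services section adds that the navigator may prompt patients to invite more relatives. The Navigator invitation section says relatives are told about the study in terms of their family's arm.

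The primary outcome and Secondary Aim 1 differ. In Table 4, both divide by the relatives the patient reported on the baseline survey, which is completed before randomization.

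**The concern.** Randomization makes the families comparable. It does not make the relatives who later enroll comparable if the arm influences who enrolls. One randomized feature includes outreach meant to raise enrollment, and Secondary Aim 1 hypothesizes that both features raise the share of relatives invited. If that succeeds, the pool from which Aim 3's denominator is drawn differs by arm.

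Suppose the relatives brought in by extra outreach are less inclined to seek evaluation. The proportion among enrollees then falls in the navigator arms even if navigation harms nobody. If they are more inclined, it rises even if navigation helps nobody. A reader who takes the aim's wording at face value would attribute either result to the intervention.

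**Working it through.** **1. The plan's own figure.** The article expects three invited relatives for each of 412 patients, and "Overall, we anticipate of those invited that 30% will enroll".

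- Invited: 412 × 3 = 1,236.
- Enrolled: 1,236 × 0.30 = 370.8, which reproduces the stated 371. (Table 2 prints 3.3 relatives per patient beside 1,236; that total corresponds to three.)

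The article states no power or target difference for Aim 3.

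**2. Sequence of events.** Baseline survey, patient enrollment, family randomization, invitation by arm-specific methods, relative enrollment, six-month survey. The denominators of the primary outcome and Secondary Aim 1 are fixed at the first step. Aim 3's denominator is fixed at the fifth.

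**3. Size of the selection effect, on assumed values.** Let e0 and e1 be enrollment among invited relatives without and with the navigator, qa the evaluation rate in those who would enroll anyway, and qe the rate in additional enrollees. With no effect on any individual:

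proportion among enrolled with navigator = [e0·qa + (e1 − e0)·qe] / e1

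spurious difference = [(e1 − e0)/e1] × (qe − qa)

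Assumptions: e0 = 30%, qa = 40%, equal numbers invited, full survey response.

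| e1 | share of additional enrollees | qe = 20% | qe = 60% |
|---|---|---|---|
| 33% | 0.03/0.33 = 9.1% | 38.2% (−1.8) | 41.8% (+1.8) |
| 36% | 0.06/0.36 = 16.7% | 36.7% (−3.3) | 43.3% (+3.3) |
| 40% | 0.10/0.40 = 25.0% | 35.0% (−5.0) | 45.0% (+5.0) |
| 45% | 0.15/0.45 = 33.3% | 33.3% (−6.7) | 46.7% (+6.7) |

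The comparison value is 40% throughout; differences are in percentage points. The difference is zero if enrollment is equal in this model, or if additional enrollees have the same rate as the others.

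The article gives 30% as the overall rate, not the rate without a navigator. Centering on it changes little. For a 3-point gap, 28.5% against 31.5% gives 0.03/0.315 × 20 = 1.9 points. For a 15-point gap, 22.5% against 37.5% gives 0.15/0.375 × 20 = 8.0 points.

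**4. The same scenario on the baseline denominator.** Each navigator level has 412/2 = 206 patients, 206 × 8 = 1,648 reported relatives and 1,236/2 = 618 invited. Take qe = 20% and count only enrolled relatives' evaluations.

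- Without navigator: 618 × 0.30 × 0.40 = 74.2, or 4.50%.
- With navigator, e1 = 36%: 618 × (0.12 + 0.012) = 81.6, or 4.95%.
- With navigator, e1 = 40%: 618 × (0.12 + 0.020) = 86.5, or 5.25%.
- With navigator, e1 = 45%: 618 × (0.12 + 0.030) = 92.7, or 5.63%.

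If the additional relatives would have been evaluated at 20% whether or not they enrolled, true evaluation in this group is equal in both arms. In the last case the excess of 92.7 − 74.2 = 18.5 is then extra documentation, not extra evaluation. The baseline denominator restores the randomized population but leaves ascertainment dependent on enrollment.

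**The case against.** **Nothing shows that enrollment differs by arm.** This is correct. Navigator contact is optional and chosen by the patient for each relative, and every invited relative eventually receives the email. A reader might infer that enrollment is known to be altered. The documents show only that the design allows and intends it.

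**The price route is inferred.** This also stands. The arm-specific description suggests that relatives see the price before enrolling, but the invitation text is not printed. The Recruitment and randomization section reports that a pilot saw no detrimental effect of the $50 offer on enrollment. It gives no figures and does not say whether the same kinds of people enrolled, so it neither removes nor confirms the price route.

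**Dramatic examples are easy to build.** If 30 of 100 invited relatives enroll with 60% evaluated, and 15 more join with 10% evaluated, the rate is (18 + 1.5)/45 = 43%, apparently 17 points worse. A reader might infer a distortion of that size, or that it must run against the navigator. The documents give none of those evaluation rates and do not fix the direction.

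**The replacement denominator has its own bias.** This is the strongest point, and it stands. Only enrolled survey responders can be recorded as evaluated, so an arm that enrolls more can look better, in the direction the trial hypothesizes. The six-month window starts at enrollment and is undefined for relatives who never enroll. Relatives clinically tested within five years cannot enroll, yet may be in the baseline count.

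**The analysis of Aim 3 may be in the supplement.** The article prints no model for this aim, and that is not held against it. The denominator is stated twice, however, and a model elsewhere would not change it.

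**Conclusion.** The point holds for Secondary Aim 3 only. As worded, the aim attaches a causal claim to a group formed after randomization whose make-up the navigator feature can change. On the assumed values, selection alone produces a difference of about 2 to 7 points in either direction. For scale, Table 5 targets 3 points for price and 5 for navigation on the primary outcome, which is a different endpoint. The illustration rests on assumed evaluation rates and enrollment gaps; the documents supply only 30% overall enrollment.

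The navigator route follows directly from the text, while the price route is plausible but unproven. A reader might extend the criticism to the primary outcome or Secondary Aim 1. Table 4 does not support that, because both count over relatives reported before randomization. This is a matter to correct before analysis, not a threat to the trial's main conclusion.

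**What to change.** 1. State that the proportion evaluated among enrolled relatives is descriptive and supports no causal claim about either feature.
2. Report relatives' enrollment and six-month survey response by arm.
3. If a between-arm comparison is wanted, divide relatives with a documented formal evaluation by the relatives reported on the baseline survey (Table 4's denominator for the primary outcome). Use the primary's binomial model with a random intercept per index patient, and label the result *documented through the study*.
4. State the downside beside it: evaluations in non-enrolled relatives and non-responders are unobserved, so an arm that enrolls more can show more documented evaluation when true evaluation is equal. Add a sensitivity analysis over assumed evaluation rates in the unobserved relatives. Say how the six-month window and previously tested relatives are handled.

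The cost is a rewording of the endpoint, one further run of a model already planned, two descriptive tables and the sensitivity analysis. No new data are needed. The Discussion says relatives are still being invited and enrolled, so the change can be fixed before their six-month survey data are complete.
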